#### Data on outcome

Outcome data is collected weekly using the Oslo Sports Trauma Research Center Questionnaire [25]. If full participation is not possible due to a perceived physical problem, the participant is contacted by telephone. If a participant reports an injury, an appointment for physical examination is made. Certified physiotherapists (the diagnostic team) perform the clinical examinations, using a previously employed standardized examination procedure [10]. Examinations are performed in the respective physiotherapeutic clinics, in which members of the diagnostic team are employed. After an examination, the physiotherapist reports data on diagnosis to the research group.

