### Outcome

The primary outcome is injury defined as a Running-Related Injury (RRI): *An injury sustained on muscles, joints, tendons and/or bones during or after running and attributed to running. The injury must have caused a training reduction (reduced distance, intensity, frequency etc.) for at least 7 days* [19], [34].

The secondary outcome is symptoms of overuse injury defined as: *A physical problem perceived as pain, tenderness, stiffness, aching, looseness, locking or instability in any part of the body* [25]. The information is collected using a modified version of the OSTRC questionnaire [25]. The modification of the questionnaire consists of an addition to the possible answers in the fourth and last question *“Cannot participate due to pain”*. The included anatomical areas are: foot, ankle, front of lower leg, calf, knee, thigh, hamstrings, groin, glutes, hip and lower back. An approach similar to the one used by Clarsen et al. [33], is applied to ease the response load on the participants.

All participants who report an RRI are referred to injury diagnosis, performed by a physiotherapist. Injury diagnosis is carried out using a standardized examination protocol and standardized diagnostic criteria [10]. The OSTRC questionnaire will continue to be administered to participants who are diagnosed with an injury, in order to explore the severity of injuries.

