### Statistical analysis

All data will be analyzed using an instrumental variable approach in the primary analysis [36]. The instrumental variable is the randomization. Secondary analyzes are intention-to-treat and per-protocol. Time to first injury is analyzed using the following primary time scale: calender time in days and weeks. Data will be analyzed at the following time-points: 2 weeks, 4 weeks, 8 weeks and 16 weeks after randomization. Secondary time scales are cumulative running volume in kilometres and cumulative running volume in minutes. Time of follow-up begins when the randomized interventions start. The unit of analysis is each participant. Participants will be right-censored in case of pregnancy, disease, lack of motivation, non-running-related injury causing a permanent stop of running, unwillingness to attend clinical examination in case of injury, if more than 10 % of all training sessions were uploaded manually (they will be censored at the time 10 % of uploads are manual) or at end of follow-up, whichever comes first.

The injury proportion as a function of the follow-up time scales mentioned above will be estimated using the Kaplan-Meier curve. The cumulative injury risk difference between groups is analyzed, performing a generalized linear regression, using the pseudo values method [37]. Competing risk analysis will be performed separately for both groups, to investigate difference in risk of hypothesized injuries including more than one endpoint [38]. The Aalen Johansen estimator will be applied in the competing risks analysis. Endpoints included in the competing risk analysis are non-running-related injury causing a permanent stop of running and the 20 injuries presented by Taunton et al. [13] In the intensity group (Sch-I) the risk of achilles tendinopathy, gastrocnemius injuries, and plantar fasciitis are analyzed in a competing risk model, treating the remaining 17 injuries as competing events. In the volume group (Sch-V) the risk of patellofemoral pain syndrome, iliotibial band syndrome, and patellar tendinopathy are analyzed in a competing risk model, treating the remaining 17 injuries as competing events [21]. Differences are considered statistically significant at *p* < .05, and estimates are presented with 95 % confidence intervals. All analyzes are performed using STATA/SE version 13 (or more if applicable).

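### Censoring runners who report an injury and then decline the examination makes censoring depend on the outcome, so probable primary events are lost

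*Protocol article*

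**What the plan says.** The Outcome section defines the primary outcome as "An injury sustained on muscles, joints, tendons and/or bones during or after running and attributed to running", with a severity threshold: "The injury must have caused a training reduction (reduced distance, intensity, frequency etc.) for at least 7 days". No examination is named in the definition. The examination comes afterwards: "All participants who report an RRI are referred to injury diagnosis, performed by a physiotherapist". Data on outcome gives the same order: "If a participant reports an injury, an appointment for physical examination is made".

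The examination is nevertheless more than a labelling step. Methods/design and Randomization describe the physiotherapists as blinded assessors of the outcome, and the examination is described under Data on outcome.

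Statistical analysis sets the endpoint: "Time to first injury is analyzed using the following primary time scale: calender time in days and weeks". The injury proportion "will be estimated using the Kaplan-Meier curve", and the risk difference between groups is obtained by "performing a generalized linear regression, using the pseudo values method". The same section lists the reasons for right-censoring, and one of them is "unwillingness to attend clinical examination in case of injury".

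**The concern.** Kaplan-Meier, and pseudo-values built on it, are valid when being censored says nothing about the event. Here censoring is triggered by a reported injury. The estimator takes a runner who has probably just reached the primary endpoint and gives that runner the future risk of someone still running uninjured.

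Two things are at stake. The injury risk in each arm is underestimated. The risk difference shrinks if refusal is equal and can move either way if it is not. Unequal refusal is conceivable: only the diagnostic team is described as blinded, runners follow a schedule they know, and the hypotheses expect different injury types in the two arms. Randomization does not protect against this, because the outcome is altered after allocation. That holds whether randomization serves as the instrument or as the basis of intention-to-treat.

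**Working it through.** **Inputs from the protocol article (Power)**
- Expected injury risk is 35 % in Sch-I and 20 % in Sch-V, so the RD is 15.0 points.
- The minimum difference is 5 %, power is 80 %, and 620 participants are needed before loss to follow-up.

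**Reproducing the stated figure.** Read as a superiority test against a 5-point margin (two-sided 5 %, unpooled variance, equal arms), the size per arm is

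n = (0.20 × 0.80 + 0.35 × 0.65) × (1.960 + 0.842)² / (0.15 − 0.05)² = 0.3875 × 7.849 / 0.01 = 304.1.

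Rounded up, this is 305 per arm or 610 in total, within 2 % of 620. The 35 % and 20 % are therefore the design's working values and a fair base for what follows. The point concerns estimation and leaves the sample size aside.

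**Assumptions not in the document**
- q is the share of injured runners in an arm who decline examination.
- Every refuser has a true RRI.
- The hazard is constant over the 16 weeks, refusers are censored at the time of injury, and there is no other censoring.

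**Formula.** With true risk p, the cumulative hazard is −ln(1 − p). Only the share (1 − q) of injuries is counted, and the rest leave the risk set at the same times. Kaplan-Meier therefore estimates

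1 − (1 − p)^(1 − q).

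For 20 % refusal this gives 1 − 0.65^0.8 = 0.2915 and 1 − 0.80^0.8 = 0.1635. A simulation at p = 0.35 and q = 0.30 gave 0.260, as the formula does.

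| Refusal Sch-I / Sch-V | Sch-I | Sch-V | RD (points) |
|---|---|---|---|
| 0 % / 0 % | 35.0 % | 20.0 % | 15.0 |
| 5 % / 5 % | 33.6 % | 19.1 % | 14.5 |
| 10 % / 10 % | 32.1 % | 18.2 % | 13.9 |
| 20 % / 20 % | 29.2 % | 16.3 % | 12.8 |
| 30 % / 10 % | 26.0 % | 18.2 % | 7.8 |
| 10 % / 30 % | 32.1 % | 14.5 % | 17.7 |

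RDs are taken from unrounded risks.

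**No true difference.** With 27.5 % risk in both arms and refusal of 10 % in Sch-I and 30 % in Sch-V, the estimates are 1 − 0.725^0.9 = 25.1 % and 1 − 0.725^0.7 = 20.2 %. This is a spurious RD of 5.0 points.

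**Does the first-to-occur clause rescue the rule?** The censoring sentence ends by taking whichever reason happens first. Refusal can only follow an injury. If the injury counted first, this reason would never operate. The rule has an effect only by replacing the event with a censoring.

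**The case against.** The strongest counter-argument is that the plan makes the examination its blinded outcome assessment, so a reader should not infer that it merely supplies the injury type. Methods/design, Data on outcome and Randomization all contradict that inference, and an examiner can help to judge tissue injury and attribution to running. This stands, but it does not save the rule. If examination is needed to confirm the event, refusal is a missing outcome at the moment when an event is most likely, and independent censoring still fails.

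A reader might also infer that known events are recoded as non-events. Neither half of that is supported.
- The appointment and the censoring reason refer to any reported injury, which is wider than an RRI. Some refusers may have had a shorter problem, or one not caused by running.
- Censoring is not the same as coding no injury. At 20 % refusal in both arms, non-event coding would give 28.0 % − 16.0 % = 12.0 points, against 12.8 under censoring.

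Third, a reader might conclude that the distortion must exceed the 1 % that the Discussion calls the minimal clinically relevant difference. It need not: 5 % refusal in both arms shifts the RD by only 0.5 point. At 20 % in both arms the shift is 2.2 points, still below the 5 % used under Power. The large shifts need threefold differences in refusal between arms, for which the document gives no evidence.

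Finally, the primary analysis is instrumental-variable, and the figures above describe a plain difference between arms.

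**Conclusion.** The point holds. One listed censoring reason depends on the outcome by its own wording, conflicts with an RRI definition that requires no examination, and violates the assumption behind both named estimators. Probable primary events are lost.

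The direction is clear within each arm: risk is underestimated to the extent that refusers are true RRIs. Equal refusal attenuates the RD, while unequal refusal can shrink or inflate it. The size cannot be known from the document. Over the assumed refusal rates the RD runs from 7.8 to 17.7 points around a true 15.0, and it lies close to 15.0 if refusal is rare and balanced. If some refusers have no RRI, the loss is smaller. The effect on the instrumental-variable estimate was not computed.

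Because the rule touches the primary endpoint and can be corrected before the data are analysed, it should be changed whatever refusal rate is expected.

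**What to change.** Changes to Statistical analysis:

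1. Delete the refusal of examination from the censoring reasons.
2. In the primary analysis, count each unexamined reported injury as an event at its onset if it meets the RRI definition (attributed to running, training reduced for 7 days or more). Someone unaware of group should judge this from the weekly questionnaire, the telephone contact and the uploaded running data.
3. Keep runners whose report does not meet the definition in follow-up.
4. Treat runners whose status cannot be determined as having a missing outcome, with sensitivity analyses that count all of them and none of them as events.
5. In the competing-risks analysis, enter unexamined RRIs as a separate endpoint, type unknown.
6. Report examiner-confirmed injuries only as a sensitivity analysis.

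The cost is a few sentences of analysis wording and a short classification rule, using data streams already planned. Two limits should be acknowledged. Some primary events will rest on self-report by unblinded runners without the blinded examiner's confirmation. Also, the article states that the weekly questionnaire continues after injury only for diagnosed runners and does not describe the content of the telephone call. The plan should confirm that both cover unexamined runners well enough to judge attribution to running and the 7-day criterion.

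### The 10 % manual-upload rule ends injury follow-up for an exposure-data reason in every analysis, including calendar-time intention-to-treat, and its denominator is not fixed

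*Protocol article*

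**What the plan says.** All of the following is in the protocol article.

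- **The rule (Statistical analysis).** One right-censoring list is given for time to first injury. A runner is censored if more than 10 % "of all training sessions were uploaded manually (they will be censored at the time" 10 % of uploads are manual). The list closes with "or at end of follow-up, whichever comes first", so an injury before the censoring date stays in as an event.
- **Time scales (same section).** "Time to first injury is analyzed using the following primary time scale: calender time in days and weeks". The scales built from running data are secondary: "Secondary time scales are cumulative running volume in kilometres and cumulative running volume in minutes".
- **Analyses (same section).** The primary analysis is instrumental-variable with randomization as the instrument. Intention-to-treat and per-protocol are secondary. The censoring list is not varied between them.
- **Outcome source (Data on outcome; Outcome).** "Outcome data is collected weekly using the Oslo Sports Trauma Research Center Questionnaire". Telephone contact and a physiotherapist's examination follow.
- **Exposure source (Data on exposure).** Running performed is recorded by smartphone GPS.
- **Schedule (Intervention).** Three sessions a week throughout, with 8 preconditioning weeks and 16 intervention weeks.

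**The concern.** Censoring is meant for runners whose injury status can no longer be observed. A runner who enters some sessions by hand still answers the questionnaire and can still be examined. Under the rule, an injury that the trial has observed and diagnosed is dropped if the 10 % mark was reached first. This also happens in the intention-to-treat analysis, which uses only allocation and injury date.

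The wording does not settle when the mark is reached. The trigger refers to sessions and the timing to uploads. One says more than 10 % and the other says 10 %. The denominator could be the sessions so far, the 48 scheduled, all those finally performed, or any of these with preconditioning included. At stake are the number of injuries that reach the analysis and, on some readings, whether the risk estimate is unbiased.

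**Working it through.** **Inputs from the protocol.** Threshold 10 %. Sessions: 3 × 16 = 48 in the intervention period and 3 × 8 = 24 in preconditioning. Expected injury incidence is 20 % and 35 % (Power), with mean (20 + 35)/2 = 27.5 %.

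**Assumptions.** The protocol gives no manual-upload rate. I take p = 1, 2, 5 and 8 % per session, independent between sessions, with a constant injury hazard giving 27.5 % risk at 16 weeks. The protocol states no figure for the effect of this rule, so there is nothing to reproduce first.

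**Step 1: what trips the rule.** With a running share from randomization, one manual upload by session 9 gives 1/9 = 11 %, above 10 %. At session 10 it gives exactly 10 %, where the two phrasings of the rule differ. By session 24 it takes 3 manual uploads (3/24 = 12.5 %), and by session 48 it takes 5 (5/48 = 10.4 %).

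**Step 2: exact probabilities.** At least one manual upload in the first 9 sessions has probability 1 − (1 − p)^9; at p = 5 % this is 1 − 0.95^9 = 37.0 %. At least 5 manual uploads of 48 is a binomial tail.

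| p | ≥ 1 in first 9 | ≥ 5 of 48 |
|---|---|---|
| 1 % | 8.6 % | 0.01 % |
| 2 % | 16.6 % | 0.3 % |
| 5 % | 37.0 % | 9.1 % |
| 8 % | 52.8 % | 33.8 % |

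**Step 3: share of 16-week injuries discarded (simulation, 200,000 runners).** An injury is discarded if the trigger came before it.

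| p | Running share from randomization | Fixed 48 (fifth manual upload) |
|---|---|---|
| 1 % | 8 % | 0 % |
| 2 % | 16 % | 0 % |
| 5 % | 37 % | 2 % |
| 8 % | 55 % | 8 % |

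If the running share also counts the 24 preconditioning sessions, a first manual upload just after randomization gives 1/25 = 4 % and does not trip the rule. About 2 % of runners are then ever censored at p = 2 % and about 23 % at p = 5 %. Without preconditioning the figures are 18 % and 46 %.

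**Step 4: timing on the running reading, p = 5 %.** Runners meeting the rule by weeks 2, 4, 8 and 16: 26.5, 37.3, 42.7 and 45.9 %. Injuries discarded among those occurring in weeks 0–2, 2–4, 4–8 and 8–16: 12, 32, 40 and 45 %. Censoring comes early, but the share of injuries lost rises with time, because the chance that the trigger has already occurred cannot fall.

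**Step 5: final share of sessions performed, with the date set back.** Runners are assumed to log nothing after injury. An early-injured runner then has a small denominator: one manual upload in 9 is 11 %, while one in 48 is 2 %. At p = 2 %, 3.1 % of injured runners are censored before their injury, against 0.3 % of uninjured runners. At p = 5 % it is 13 % against 9 %. Injuries lost in the four periods at p = 5 %: 11, 24, 15 and 10 %. The Kaplan-Meier risk at p = 5 % is 24.8 to 26.0 %, depending on how the date is set back, against a true 27.5 %, although uploading is unrelated to risk.

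**Step 6: bias on the running reading.** With uploading unrelated to risk, Kaplan-Meier returns 27.5 % against 27.5 %. Now suppose 30 % of runners upload manually in 15 % of sessions and the rest in 1 %. If the first group has 0.5, 1.5 or 2 times the risk of the others, the estimate is 31.0, 24.8 or 23.0 % against about 27.5 %. These inputs are illustrative.

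**The case against.** **The rule has a purpose.** The primary instrumental-variable analysis needs a measure of running received, and that comes from GPS. A reader might infer that the primary analysis has no use for GPS data because its time scale is calendar time; that holds for injury ascertainment and for intention-to-treat, but not for this analysis. The objection stands that far. Poor exposure data is a reason to treat the exposure as missing or mismeasured. It is not a reason to stop counting injuries, and it gives no ground for censoring in intention-to-treat.

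**The text may already mean 48.** The trigger speaks of all training sessions and the schedule fixes 48 of them. The loss is then nil or small up to p = 5 %. This reading is possible and a large loss is not demonstrated. But the timing clause counts uploads, and nothing chooses between the readings.

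**The losses do not show bias.** This is correct for the running and fixed readings under random uploading (Step 6).

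**Conclusion.** The concern holds in this form: a stated rule ends injury follow-up for an exposure-upload reason in every analysis, with no exemption for calendar-time intention-to-treat and no fixed denominator. That rests on the text alone. The size rests on assumed upload rates and on the reading. At 5 %, about 37 % of injuries are lost with a running share from randomization, and about 2 % with a fixed 48.

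Two stronger readings are not supported. One might infer that the rule mainly removes early injuries. On the running and fixed readings the share lost is smallest in the first two weeks and largest late; only the final-share reading concentrates the loss earlier, in weeks 2–4 at 2 % and 5 %, and the protocol does not state that denominator. One might also infer that the censoring is shown to be informative. It depends on the outcome on the final-share reading. On the other two it may be informative if manual uploading is related to injury risk, and may differ by arm if one schedule produces more manual uploads, but the protocol gives no data on either.

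**What to change.** - **Calendar-time scale:** take the manual-upload reason off the censoring list, at least for intention-to-treat. Keep these runners at risk until injury, another listed censoring reason or 16 weeks.
- **Instrumental-variable analysis:** keep the injury outcome, treat the affected exposure as mismeasured or missing, and add a sensitivity analysis.
- **Kilometre and minute scales, and per-protocol:** retain the 10 % rule there, with a fixed denominator of 48 scheduled sessions, so that the fifth manual upload triggers it.

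The cost is a sentence or two of analysis wording and no new data, since the questionnaire and examinations continue anyway. The small downside is that measures of running received will rest partly on manual entries for these runners.

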### Power

The power calculation was based on a superiority calculation. Based on comparisons between the current and previous studies, considering differences between populations and interventions, and including experiences from clinical practice, an injury incidence of 20 % is expected in runners focusing on volume and an injury incidence of 35 % is expected in runners focusing on intensity [18, 19]. To be able to show a minimum difference in injury risk between groups of 5 %, a sample size of 620 participants is required to reach a power of 80 %. An accommodation to a potential loss to follow-up is necessary to include in determining the number of participants needed. In prospective studies with a self-structured running regime and a follow-up ≥ 6 months, the loss to follow-up have been reported to be approximately 22–30 % [34, 35]. Prospective studies with a structured running regime, and follow-up periods of 13 weeks, reported the loss to follow-up to be approximately 8 and a 60 % completion of the scheduled running [12, 19]. Taking into consideration the duration of the 24-week follow-up period in the present study, and the motivational factor possibly associated with a structured running regime, a potential loss to follow-up of 15 % is hypothesized, which leads to a required sample size of 713 participants.

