### Complementary risk factor analysis

To study if the effect of the intervention on the risk of RRI were modified by running experience, BMI, gender, previous injury, age and general activity level, a stratified analysis in accordance with the recommendations by Knol, *MJ* and Vanderweele, *TJ* [39] will be performed. All predictor variables will be included in the stratified analysis, provided that the recommendation of at least 10 injuries per predictor variable is fulfilled [40].

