## Discussion

Run Clever is the first randomized trial to investigate how a running schedule focused on running intensity compared with a running schedule focused on running volume influences the overall risk of injury and the type of injuries sustained.

The population of interest is rapidly growing and should be prioritized, as it possibly is the largest group of recreational active adults worldwide [1, 41]. Recreational runners as a group are characterized by a large heterogeneity, especially concerning running experience and training habits. Consensus regarding the definition of a recreational runner is not established and the term is used inconsistently in relation to a wide variety of running populations. In three studies all describing the included runners as recreational, running experience in years ranged from 5.0 to 8.6 and the weekly volume in kilometers ranged from 28 to 38. However, the weekly running frequency only ranged from 3.0 to 3.8 [35, 42, 43]. The present trial defines the population as recreational runners, using the inclusion criteria of an average weekly frequency between 1 and 3 running sessions the past 6 months. The choice of weekly frequency was primarily based on a descriptive study by the Danish Institute for Sports Studies, which showed that the largest proportion of recreational runners in Denmark averaged 1 – 3 weekly running sessions [44].

The ideal percentage of weekly progression is unclear and a trial by Buist et al. comparing a weekly progression of 10.5 and 23.7 % found no difference in risk of RRI. However, a weekly progression of 30 % has been found to increase the risk of specific RRI [19, 24]. In an attempt to allow for adaptation to the progression in running, the research team developed the 4-week cycle, based on a theoretical step loading approach [29].

The follow-up Run Clever applies, aims at increasing the homogeneity of the included participants, in relation to the running performed most recently, prior to allocation to the intervention. Other running-related factors, such as running experience and previous running-related injury, are non-modifiable parts of the heterogeneity characterizing recreational runners, and can only be sought controlled for through the baseline data collection and complementary risk factor analysis.

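### No covariate adjustment is stated for the primary risk difference, and control of prognostic differences is left to an effect-modification analysis: a modest, cheap loss of efficiency

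*Protocol article*

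**What the plan says.** The Statistical analysis section of the protocol article makes an instrumental-variable analysis primary, with randomisation as the instrument, and puts intention-to-treat and per-protocol analyses second. The effect measure is described in one sentence: "The cumulative injury risk difference between groups is analyzed, performing a generalized linear regression, using the pseudo values method". No covariate is named there. The word unadjusted does not appear either.

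The Baseline measurements section shows that demographics, medical history, running experience, BMI, overuse symptoms (OSTRC) and habitual activity (SQUASH) are all recorded before training starts. Their stated use is in the Complementary risk factor analysis section, which asks whether the intervention effect is modified by "running experience, BMI, gender, previous injury, age and general activity level", using stratified analyses.

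The Discussion gives running experience and previous injury as examples of differences between runners that "can only be sought controlled for through the baseline data collection and complementary risk factor analysis". The Randomization section describes equal group sizes but no stratification factors.

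**The concern.** The Discussion speaks of control and points to one named analysis for it. That analysis, as its own section defines it, compares the intervention effect across strata. It may show whether the effect differs by experience or previous injury, but it leaves the overall group contrast as it was. Nothing in the article therefore uses the baseline predictors to sharpen the primary estimate or to remove chance imbalance in them, and stratified randomisation is not described as an alternative.

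What is at stake is precision. The predictors are already collected, a regression on pseudo-values accepts covariates directly, and with an identity link and main effects only the group coefficient is still a risk difference. Recruitment stops after six months whatever the number reached, so precision that costs no extra participants has some value.

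**Working it through.** **Inputs from the protocol article**
- Schedule-V: "an injury incidence of 20 % is expected in runners focusing on volume". Schedule-I: "an injury incidence of 35 % is expected in runners focusing on intensity" (Power).
- Margin: "To be able to show a minimum difference in injury risk between groups of 5", read as percentage points (Power).
- Size and power: "a sample size of 620 participants is required to reach a power of 80" per cent (Power); fallback of 357 with a 1-point minimum difference and 15 % loss (Discussion).
- Significance: "Differences are considered statistically significant at *p* < .05" (Statistical analysis). Sidedness is not stated; two-sided reproduces the figures.
- Assumption: the covariates explain R² = 0.02 to 0.15 of outcome variance. The article gives no figure.

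**Step 1: reproduce the plan's sizes without covariates.** With V = 0.35 × 0.65 + 0.20 × 0.80 = 0.3875 and (1.96 + 0.8416)² = 7.849:
- 5-point margin: n per arm = 0.3875 × 7.849 / (0.15 − 0.05)² = 304.1, so N = 610 against the stated 620 (1.6 % apart).
- 1-point margin: n per arm = 0.3875 × 7.849 / (0.15 − 0.01)² = 155.2, so N ≈ 310, and 310 × 1.15 = 357, as stated.

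Both stated sizes therefore follow from the article's own inputs with no adjustment.

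**Step 2: precision without adjustment.** SE = √(0.3875 / n).
- 310 per arm: SE = 3.54 points, half-width = 1.96 × 3.54 = 6.9 points.
- 155 per arm (357 / 1.15): SE = 5.00 points, half-width 9.8 points.
- 151.7 per arm (357 × 0.85 = 303 evaluable): SE = 5.05 points, half-width 9.9 points.

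**Step 3: with adjustment.** The variance is multiplied by (1 − R²), which is worth a factor 1/(1 − R²) in sample size. Power = Φ((15 − margin)/SE − 1.96).

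| Assumed R² | 0 | 0.02 | 0.05 | 0.10 | 0.15 |
|---|---|---|---|---|---|
| Equivalent extra participants, % | 0 | 2 | 5 | 11 | 18 |
| Half-width, 620 evaluable, points | 6.9 | 6.9 | 6.8 | 6.6 | 6.4 |
| Half-width, 310 evaluable, points | 9.8 | 9.7 | 9.6 | 9.3 | 9.0 |
| Half-width, 303 evaluable, points | 9.9 | 9.8 | 9.7 | 9.4 | 9.1 |
| Power, 620, 5-point margin, % | 80.7 | 81.5 | 82.7 | 84.6 | 86.6 |
| Power, 303, 1-point margin, % | 79.1 | 79.9 | 81.1 | 83.2 | 85.2 |
| Power, 303, 5-point margin, % | 50.7 | 51.6 | 52.8 | 55.0 | 57.4 |

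To judge how plausible the R² range is: with one normally distributed risk score and 27.5 % overall risk, R² of 0.03, 0.06, 0.11 and 0.15 correspond to an AUC of about 0.61, 0.66, 0.70 and 0.74. The top of the range needs fairly good prediction.

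**Step 4: events available.** Assume constant hazard and the stated risks at 16 weeks. The risk by week t is then 1 − (1 − p)^(t/16), averaged over the two arms. With 303 evaluable this gives about 12, 24, 45 and 83 injuries by weeks 2, 4, 8 and 16. Six single-parameter covariates plus group make seven terms. At ten injuries per term, the yardstick the article sets for its stratified analysis, 70 are needed. At the fallback size only the 16-week analysis reaches that.

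**Scope.** These figures are for the intention-to-treat type contrast with complete data among those evaluable. The instrumental-variable interval will be wider under non-adherence; the proportional saving from adjustment should be similar.

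**The case against.** The strongest reply is that this is an argument from silence. The article is a condensed account, a covariate list is commonly left to the analysis plan, and a generalised linear model on pseudo-values may well contain covariates. That stands in part: a reader might infer that the protocol declares the primary model unadjusted, and it does not. But the text is not wholly silent, because the Discussion names where control is to happen, and the named analysis does not supply it for the primary contrast.

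A second reply is that the Discussion sentence admits a limitation and sets no requirement. That is right. A reader might infer that the plan breaks its own demand for control; the wording does not support this, and it gives only running experience and previous injury as examples.

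Third, the gain is small and its size is assumed. This also stands. At R² = 0.02 it is negligible, and one likely predictor is weakened because people with a lower-extremity injury in the six months before baseline are excluded.

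Fourth, too many covariates would strain the early time points. The event counts above bear this out at 2 and 4 weeks, and at 8 weeks for the fallback size, so the list should be short and the requirement limited to the 16-week estimate where events are few.

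**Conclusion.** The point holds as a suggestion for efficiency. No adjustment is stated, and the analysis to which control is assigned is a stratified effect-modification analysis. The unadjusted randomised comparison remains valid, and the absence of stratified randomisation is no error. Under an assumed R² of 0.02 to 0.15, the benefit equals about 2 to 18 % more participants, or at most about 0.5 points of half-width at 620 and about 0.8 points at the fallback.

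Two stronger readings should be resisted:

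- A reader might infer that the fallback of 357 depends on adjustment, or would be rescued by it. On its own 1-point margin it already has about 79 to 80 % power unadjusted. Against the 5-point margin it has about 51 %, and adjustment lifts that only to 52–57 %. The shortfall comes from the change of margin.
- A reader might infer that adjustment also protects against dropout related to these factors. It does not: pseudo-values computed from the marginal Kaplan-Meier estimate still require censoring to be independent of the covariates, and adding regressors leaves those pseudo-values unchanged.

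**What to change.** State whether the primary models are adjusted, and prespecify a short list of pre-allocation covariates as main effects: for example previous injury, running experience, age, gender, BMI and the OSTRC score. Enter them in the pseudo-value regression and in both stages of the instrumental-variable model, at least for the 16-week estimate. Keep the unadjusted result as a sensitivity analysis.

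Use the OSTRC score from baseline 1 unless it is confirmed that allocation follows baseline 2. The Methods/design section places randomisation after the preconditioning period, while the Randomization section places allocation at inclusion.

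Reword the Discussion so that control of prognostic differences is tied to the adjusted primary model, and the complementary analysis is described as effect modification only.

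The cost is a few sentences and slightly more analysis work, with no new data. The drawback is sparse events at 2 and 4 weeks, where the unadjusted estimate can stand.
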